## Abstract

**Background:**

ED overcrowding represents a significant public health problem in developed countries. Frequent users of the emergency departments (FUEDs; reporting 5 or more ED visits in the past year) are often affected by medical, psychological, social, and substance use problems and account for a disproportionately high number of ED visits. Past research indicates that case management (CM) interventions are a promising way to reduce ED overcrowding and improve FUEDs’ quality of life. There is, however, very limited knowledge about how to disseminate and implement this intervention on a large scale to diverse clinical settings, including community hospitals and non-academic centers. This paper describes the protocol of a research project aiming to implement a CM intervention tailored to FUEDs in the public hospitals with ED in the French-speaking region of Switzerland and evaluate both the implementation process and effectiveness of the CM intervention.

**Methods:**

This research project uses a hybrid study design assessing both implementation and clinical outcomes. The implementation part of the study uses mixed methods a) to describe quantitatively and qualitatively factors that influence the implementation process, and b) to examine implementation effectiveness. The clinical part of the study uses a within-subject design (pre-post intervention) to evaluate participants’ trajectories on clinical variables (e.g., quality of life, ED use) after receiving the CM intervention. We designed the study based on two implementation science frameworks. The Generic Implementation Framework guided the overall research protocol design, whereas the RE-AIM (reach, efficacy, adoption, implementation and maintenance) framework guided the implementation and effectiveness evaluations.

**Discussion:**

This research project will contribute to implementation science by providing key insights into the processes of implementing CM into broader practice. This research project is also likely to have both clinical and public health implications.

**Trial registration:**

NCT03641274, Registered 20 August 2018.

## Background

ED overcrowding is a common public-health concern in developed countries impacting both patients and health system outcomes [1]. For instance, there are over 1.4 million annual ED visits in Switzerland (8.5 million inhabitants) with 84% of EDs reporting overcrowding [2]. Frequent users of the emergency departments (i.e., FUEDs; reporting 5 or more ED visits in the past year) [3] are in need of targeted attention from clinicians, public health advisors and researchers. FUEDs disproportionately access ED services, and contribute to ED overcrowding (i.e., FUEDs account for 3 to 8% of all patients and 12 to 28% of all ED visits) [4–6]. Driving this high use of health care services is the fact that FUEDs are often affected by multiple chronic medical diseases (e.g., heart disease, cancer) [7–9], as well as psychiatric, substance use and social problems (e.g., unemployment or social isolation) [4, 10–12]. In response, important research efforts have been dedicated to identify, develop and test interventions tailored to this population, such as case management (CM) intervention. Past research has found CM intervention as a promising way to reduce ED overcrowding and improve FUEDs’ quality of life [3, 12–16]. However, there is limited knowledge about how to disseminate and implement such an intervention on a large scale to diverse clinical settings, including community hospitals and non-academic centers. Implementation science provides a framework for integrating evidence-based interventions, such as the CM intervention, in real-world settings while evaluating their feasibility, acceptability and effectiveness over the implementation process. In this article, we describe the protocol of a study funded by the Swiss National Science Foundation (FNS 407440_167341) that aims to implement a CM intervention for FUEDs in several hospitals in the French-speaking region of Switzerland.

### The evidence-based practice being implemented

In line with FUEDs’ specific needs, the CM intervention aims at redirecting and reorienting FUEDs to a range of services within the hospital and community-based settings to improve the quality of care for these patients and reduce the ED overcrowding that negatively impacts all ED patients [12]. The CM intervention targets several mechanisms through which the CM intervention is expected to decrease FUEDs ED visits and related costs and to increase their quality of life. In addition to cares coordination, these mechanisms include health care empowerment (i.e., being engaged, informed, collaborative and committed to one’s health care) [17], perceived self-efficacy (i.e., the belief in one’s ability to perform a task) [18], and health literacy (i.e., skills to meet the complex demands related to health) [19].

Building on previous findings related to CM effectiveness [12], our research team developed and tested a CM intervention tailored to FUEDs in Lausanne University Hospital [3, 20]. Based on FUEDs needs and characteristics [21, 22] this intervention targets several specific components. First, the case managers provide counseling and education on health care utilization, substance abuse and the social determinants of health related to FUEDs, using skills such as motivational interviewing and cross-cultural competences [23, 24]. Additionally, the case managers enable access to concrete services, such as social services (i.e., providing support on income assistance, stable housing, improved health insurance coverage), and refer FUEDs to psychiatric, substance abuse treatment, and/or medical services (e.g., GP or medical specialist) on a case-by-case basis. Another key element of the CM intervention is to connect all health care or social service providers within the hospital and in the community, promoting continuity of care and improving the FUEDs’ ability to navigate the complex health care system. Along with this key dimension of the CM intervention, case managers send on a case-by-case basis letters summing up their intervention to FUEDs’ general practitioners or other involved health-care providers.

### Case management intervention effectiveness

Previous research among FUEDs has established CM intervention effectiveness in improving housing and environmental quality of life and reducing homelessness [12, 13]. There is however, mixed evidence of CM intervention effectiveness in reducing ED use. On one hand, systematic reviews conducted in 2011 [12] and 2016 [14] on interventions including CM, care navigation, patient education and disease specific management programs, found that CM intervention only consistently reduced frequent ED use. On the other hand, results yielded in the few randomized clinical trials conducted to date are mixed [3, 15, 25, 26]. For instance, a recent randomized clinical trial conducted by our research team tested CM intervention efficacy [3]. FUEDs were randomized to the CM intervention or control groups. After 12 months, participants in the intervention group made 2.71 (+/− 0.23) ED visits versus 3.35 (+/− 0.32) visits in the control group (ratio 0.81, 95% CI 0.63–1.02), corresponding to a 19% absolute reduction in ED use. Of important note however, findings indicated that CM intervention effect on the number of ED visits was not significant. Therefore, although most findings support CM intervention effectiveness in reducing ED use and improving FUED’s quality of life, research further evaluating these questions is needed. Accordingly, we selected a hybrid design for this current study, examining both implementation and clinical outcomes [27].

### The guiding implementation science framework

Numerous conceptual frameworks exist to guide the design of research aiming to implement evidence-based practices in real-world settings. In this study, we used the Generic Implementation Framework [28] to guide the overall research protocol design and the RE-AIM (reach, efficacy, adoption, implementation and maintenance) [29] framework to guide the implementation outcomes evaluation.

#### The generic implementation framework (GIF)

The GIF was developed based on a systematic review of the literature on conceptual implementation frameworks and aimed to provide guidance on the basic components required in implementation [28]. According to the GIF, implementation is a non-linear, iterative process, but may be divided into several stages (i.e., development, exploration, preparation, operation and sustainability). At each stage, specific factors strategies and evaluations influence the implementation process. Specific factors (i.e., influencing factors) include barriers and facilitators influencing the implementation process, such as health-care providers’ attitudes toward the intervention being implemented or organizational readiness to change [30]. Strategies refer to implementation interventions (e.g., clinical staff training) to assist the implementation process, whereas evaluations occur to assess the implementation process and outcomes along with the evaluation of the evidence-based intervention (i.e., the CM intervention) outcomes. Influencing factors, strategies and evaluations depend on the evidence-based intervention being implemented and the context in which it is being implemented. They also vary across settings and throughout stages of the implementation process. Finally, according to the GIF, influencing factors exist at multiple levels (e.g., individual or organizational). Therefore, strategies and evaluations should target numerous levels. We chose the GIF to develop the current implementation protocol to ensure covering the core implementation concepts. Each core component of the GIF was tailored to the current research project, in particular to the CM intervention being implemented and to the settings in which it is being implemented.

#### The RE-AIM framework

In addition to the GIF, we used the RE-AIM framework to guide the implementation and effectiveness evaluations [29]. According to the RE-AIM framework, implementation effectiveness depends on five factors: reach, effectiveness, adoption, implementation and maintenance. Reach refers to the participation rate and representativeness of the population targeted by the intervention (i.e., number of patients receiving the intervention divided by the total number of targeted patients), whereas effectiveness refers to the impact of the intervention (at the patient-level). Adoption relates to the proportion of targeted settings adopting the intervention being implemented. Implementation refers to the fidelity with which the intervention is being delivered in the real-world setting (as compared with the evidence-based intervention as it was originally designed). Finally, maintenance refers to the extent to which an evidence-based practice is integrated and sustained in real-world settings over time. Accordingly, the proposed evaluation embedded in the current study protocol targets these five factors.

### Aims of the study

To the best of the authors’ knowledge, no previous study has focused on the implementation of a CM intervention for FUEDs in Switzerland. French-speaking Switzerland includes 7 cantons and covers 23% of the extension of the country (with 2 million persons in 2015). ED overuse is of practical concern to public health advisors and clinicians. Research focusing on both implementation and clinical outcomes may provide key insights into the mechanisms and processes for disseminating and implementing a CM intervention for FUEDs into broader practice in the real-world settings. This study aims at 1) implementing a CM intervention for FUEDs in public hospitals with EDs in the French-speaking region of Switzerland, 2) studying the process of implementation of the intervention and, 3) studying CM intervention’s effectiveness among FUEDs. Regarding the intervention effectiveness assessment, we expect that FUEDs will evince improvements in clinical outcomes (e.g., higher scores in quality of life) and decreases in ED visits after receiving the CM intervention.

## Methods and design

### Design

This research project features a Type 2-hybrid study design focusing on both implementation and clinical outcomes [27]. The implementation part of the study uses mixed methods a) to describe both qualitatively and quantitatively factors that may influence implementation process and b) to assess implementation outcomes. The clinical part of the study uses a within-subject design (pre-post intervention) to evaluate participants’ trajectories after receiving the CM intervention.

### Setting

All community and academic public hospitals with an adult ED opened 24 h/ 7 days per week throughout the French-speaking region of Switzerland interested in implementing the CM intervention are eligible. There are no exclusion criteria.

### Participants

Patients visiting the ED implementing the CM intervention are eligible if they are ≥18 years, able to communicate in a language that is spoken by the local team or a professional interpreter and have ≥5 ED visits in the past 12 months recorded. Exclusion criteria include presenting less than 2 vulnerability dimensions (i.e., social, somatic, mental, risk behaviors) besides frequent ED use, being unable to give informed consent, planning to stay in Switzerland less than 18 months, not expected to survive at least 18 months, awaiting for incarceration or being currently incarcerated, having a family member already enrolled in the study.

Given that this research study aims to disseminate and implement a CM intervention, we are neither aware of the number of hospitals that will eventually participate, nor of the number of participants who will be enrolled in each hospital.

### The CM intervention

The CM intervention, as developed by our research team, typically includes the following steps. First, health-care providers and/or administrative staff detect FUEDs in the ED through an electronic alert in patients’ files. They then notify the case manager that a FUED is in the ED. Next, if the FUED visiting the ED agrees to do so, the case manager makes a first evaluation of the FUED’s situation in the ED, aiming to identify his main problems, the involved health-care network and the priorities that need to be addressed. After this first contact and if the FUED agrees ambulatory care, the case manager writes an intervention report and sets an appointment with the patient. Notably, case managers send on a case-by-case basis letters summing up their intervention to FUEDs’ general practitioner or other involved physicians. Ambulatory care consists of setting a number of appointments with the case manager on a case-by-case basis (in the ED, in the community or health-care network, or at the patient’s home depending on situation and needs). Concretely, the case manager, together with the patient, identifies objectives based on the patient’s specific needs, which will define the total number of appointments needed. Ambulatory care aims at reaching these objectives through appointments with the involved health-care network and referral to specialized services fitting the patient’s needs. Staff involved in this step include the case manager, specialized workers from the health-care network, and sometimes, the patient’s relatives. Whenever possible, the patient is asked to be active in the decisions taken to address his social and medical needs (patient empowerment). The intervention concludes when the patient is integrated into a coordinated and functional health-care network.

### Study procedure, implementation strategies and ethics

The whole project should be completed in 3.5 years over five phases (see Fig. 1). We present below the study procedure over the five phases. Table 1 presents a summary of the implementation strategies by phase. We will use hereafter the term I-CaM research team to refer to staff working on the research project in the home institution, including 2 research assistants (bachelor-level students in Medicine or Social Sciences), a research nurse (nurse, MPH), a scientific collaborator (Ph.D), and the research project leader ([name], MSc).

**Table 1 Tab1:** Description of the Implementation Program Components by Phase

Implementation program components	Description	Implementation phase	ED staff involvement
Needs and interest assessment	I-CaM team sends a survey to all eligible hospitals to assess health-providers needs and interests regarding the CM intervention.	Exploration	10 min
Hospital orientation	I-CaM team meets with key ED staff to provide more information about the CM intervention and the study procedures.	Exploration	2 h
Workshop	Interested key ED staff participate in a one-day workshop aiming to provide basic training on the CM intervention and assist in their decision of whether to adopt the CM intervention	Exploration	1 day
CM toolkit	The CM toolkit includes a detailed description of the CM intervention components, a validated framework of vulnerability among FUEDs to use as a screening tool and a booklet with practical information to use as models for the implementing sites.	Preparation, operation and sustainability	Continued use
Team member selection support	Provides a description of key team member characteristics to support team member selection at implementing sites	Preparation	Continued use
Site visits & training	I-CaM team meets with key staff in implementing sites to provide support to establish available resources on-site, to tailor the CM intervention to local realities and to provide training and coaching regarding the CM intervention to the full CM team	Preparation	2 visits of 2 h
Coaching, technical assistance & feedback	The I-CaM coach (I-CaM research nurse) conducts site visits every three months with as needed support to provide tailored assistance and feedback to each site	Operation	Between 4 and 8 h depending on sites’ needs
Coaching	The I-CaM coach provides support and technical assistance upon request from implementing sites	Sustainability	Depending on sites’ needs

#### The development and exploration phases

The I-CaM research team will develop a CM Toolkit, the team member selection-support materials and the informational announcement to be disseminated to eligible hospitals. The I-CaM research team will also develop and send by email a survey aiming to gauge interest and needs regarding the CM intervention to all eligible hospitals (to head physicians of EDs). The survey will include around 20 closed and opened-ended items addressing awareness, perceptions and knowledge of the FUED problematic as well as specific needs and interest regarding the CM. For instance participants will be asked to indicate how often they faced FUEDs over the past 2 years using a Likert scale ranging from 0 = never to 5 = every day, or to describe the main FUED-related difficulties they encounter. Results will be analyzed using both descriptive statistics and qualitative content analysis. Based on the survey results, the I-CaM research team will reach out to the interest hospitals’ key staff to provide more information about the CM intervention and the study procedures. After the meeting, key hospital staff being still interested in the CM intervention will participate in a one-day workshop at the home institution, during which they will receive basic training on the CM intervention, motivational interviewing [24], cross-cultural competencies [23] and on the study procedures, complete a questionnaire and participate in a semi-structured interview. After the workshop, all sites deciding to adopt the CM intervention will be eligible to participate in the study. Finally, hospitals not interested in participating in the study will be proposed participate in a semi-structured interview aiming to evaluate barriers to CM intervention implementation (face-to-face or by phone, depending upon possibilities).

#### The preparation phase

Sites included in the study will prepare for implementation of the CM intervention using the CM toolkit they received at the one-day workshop; with I-CaM research team support, sites will first identify CM intervention team members, including strategic and operational champions and case managers. The champions will a) promote the implementation project within the hospital, b) support its implementation and application and, c) supervise case managers who will be in charge of the CM intervention administration. Next, available resources will be established at each site and data collection systems will be finalized to gather data on implementation and clinical outcomes. The I-CaM research team will also conduct clinical and research trainings (i.e., on the informed consent process and data collection required for the research) to case managers. Finally, at the end of the preparation phase, champions and clinicians involved in the project on-site will complete a questionnaire.

#### The operation phase

The CM intervention will be implemented at all sites included in the study. First, case managers will conduct a screening process to identify eligible participants. At each site, patients fulfilling the inclusion criteria will be contacted by the case managers. The number of participants included will depend upon each site resources. We expect that each site will include at least 2 participants per week on average. The maximum number of inclusions per week per site will be discussed with the research nurse (from I-CaM staff) in charge of the clinical training and supervision in order to avoid inducing work overload. If possible (depending upon resources on each site), eligible patients having been treated in the ED in the 10 days prior the recruitment window will be contacted by phone and proposed to come back to the ED to participate in the study. Remaining FUEDs (i.e., the FUEDs not invited to participate in the study) will receive usual care.

When first meeting the participant, the case managers will present the study and examine the exclusion criterion. If the patient does not have any exclusion criteria and is interested in participating, the case managers will conduct the informed consent process. After providing written consent, participants will receive the CM intervention. After each inclusion on site, the case managers will up-date the I-CaM research team in charge of the clinical assessment (i.e., baseline and follow-up assessments of the health-related variables to describe participants’ trajectories). The I-CaM research team will contact participants and conduct the baseline assessment within 10 days following the inclusion. Participants will then complete follow-up assessments at 3, 6 and 12 months post-baseline. All assessment interviews will be conducted by phone by bachelor-level students (i.e., of medical or social sciences) who will be trained and weekly supervised. For all patients, incentives (i.e., gift cards of 10, 20 and 20 CHF for the 3, 6 and 12-month follow-ups, respectively) and reminders will be used to compensate participation and obtain good retention rates. Other clinical variables (see measures section) will be directly extracted from medical records on-site by the I-CaM research team. Each site implementing the CM intervention will monitor their activities (e.g., tracking the number of eligible patients and the number who received the CM intervention). At the end of the operation phase, the research team will conduct semi–structured interviews with case managers and champions. Both champions and case managers will also complete a questionnaire.

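### The baseline interview may follow the start of case management by some days, so a pre-intervention value for quality of life and the mechanism outcomes is not guaranteed

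*Protocol article*

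**What the plan says.** The Design section of the protocol article describes the clinical part as a "within-subject design (pre-post intervention") and names no comparison group for it. The analysis plan for clinical outcomes estimates the effect of time after CM in multilevel models.

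The section on the operation phase sets the order of events:

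1. The case manager meets the patient, checks the exclusion criteria and takes consent. Then: "After providing written consent, participants will receive the CM intervention".
2. The research team learns of the participant from the site: "After each inclusion on site, the case managers will up-date the I-CaM research team in charge of the clinical assessment".
3. The baseline interview comes next: "The I-CaM research team will contact participants and conduct the baseline assessment within 10 days following the inclusion".
4. The follow-up clock starts at that interview: "Participants will then complete follow-up assessments at 3, 6 and 12 months post-baseline".

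The interviews are separate from the site visit: "All assessment interviews will be conducted by phone by bachelor-level students".

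The section on the CM intervention describes the first contact in the ED as a CM step. The case manager evaluates problems, care network and priorities, and after this contact, if the patient agrees to ambulatory care, "the case manager writes an intervention report and sets an appointment with the patient". Ambulatory care then runs over several appointments.

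**The concern.** In a single-group pre-post design the baseline measurement takes the place of a control group. If some participants have already had CM contact when it is taken, part of any early effect sits in the value against which change is measured.

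The exposed outcomes are those collected by telephone. They are quality of life, which the Clinical measures section lists as a main outcome, and the secondary outcomes of empowerment, self-efficacy, health literacy and motivation to change. CM is meant to act on these mechanisms, and its described components include counselling, education and motivational interviewing. The rulers on alcohol change (importance, intentions, readiness, confidence) are the kind of measure that such a conversation could shift early.

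The delay can differ between participants and sites, so the amount absorbed can differ too. Without the relevant dates it could be neither measured nor adjusted for later. The Limitations section discusses regression to the mean, self-report bias and missing data, but not the timing of baseline.

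**Working it through.** **Order of events.** The article gives no figure to reproduce here; the point rests on sequence. The interview is triggered by the case manager's notice, which is sent after inclusion. So it follows consent and the first case-manager meeting. It may fall anywhere from day 0 to day 10 after inclusion. No section holds CM back until the interview, and none requires the interview to precede the next CM contact. The section on vulnerability determinants says that these are assessed during case management and extracted at baseline. This fits with CM being under way around then, but it does not date the telephone interview.

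**Length of the window.** Ten days as a share of each follow-up interval:

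- 3 months: 10/91 = 11.0%
- 6 months: 10/182 = 5.5%
- 12 months: 10/365 = 2.7%

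**What could be lost (illustration only).** Let E(t) be the CM effect t days after CM starts, d the delay from CM start to interview, and T the planned follow-up interval. Follow-up falls at d + T because it is counted from the interview. The share of the change over T that the pre-post contrast still captures is

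share = [E(d + T) − E(d)] / E(T).

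*Linear build-up*, E(t) proportional to t throughout follow-up: share = [(d + T) − d]/T = 1. Nothing is lost.

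*Saturating build-up*, E(t) = 1 − exp(−t/τ): the share reduces to exp(−d/τ), whatever T is.

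| Assumed τ (days) | Share at d = 5 | Share at d = 10 | Loss at d = 10 |
|---|---|---|---|
| 14 | 0.70 | 0.49 | 51% |
| 30 | 0.85 | 0.72 | 28% |
| 90 | 0.95 | 0.90 | about 10% |
| 180 | 0.97 | 0.95 | 5% |

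With d = 0 the share is 1.00 in every row. The values of τ are assumptions, since the document gives no time course for the effect. Taking d = 10 also assumes that CM starts on the day of inclusion and that the call is made on the last permitted day.

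**ED visits.** These are look-back counts from medical records over the past 6 and 12 months, not interview answers. The article does not say whether the baseline window ends at inclusion or at the interview, so no contamination of this outcome is shown.

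**The case against.** The strongest reply is that the article does not show substantive CM to be under way at the interview. The ten days are a maximum and run from inclusion. No CM start date is given. The first contact consists of an evaluation, a report and an appointment; work towards the patient's objectives belongs to the later ambulatory care. Counselling and motivational interviewing are listed as components without any timing. CM is also a process of several appointments, which makes slow build-up and little loss plausible. All of this stands, and it limits the claim to a pre-CM value that is not guaranteed. A reader might infer that no participant has a usable pre-CM measurement, but the text does not support that.

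A second reply is that early benefit absorbed into baseline works against finding an effect, whereas regression to the mean, which the article acknowledges, works in favour of it. The article also promises caution in interpreting changes. The directions are as stated, if the early effect is a benefit, but nothing shows that the two biases cancel.

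A reader might also extend the concern to the ED-visit counts. That would require the look-back windows to end at the interview date, which the article does not say and may reasonably leave to a fuller document.

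Finally, a reader might suggest giving the questionnaire at the consent meeting. That would usually measure quality of life during an ED visit and could worsen regression to the mean. It would also differ in mode from the telephone follow-ups and add work for site staff, whose overload the protocol seeks to avoid.

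**Conclusion.** The point holds in a limited form. The article itself fixes the order of consent, CM, notice and interview, and it does not protect the pre-CM measurement that its pre-post contrast assumes. This is therefore not a detail left to an unseen document. It concerns quality of life and the secondary mechanism outcomes; for ED visits nothing is established.

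Confidence is high on the order of events. The size is unknown: none under linear build-up, and about 5% to 51% of the change at day 10 under the assumed saturating curves, less for earlier calls. Any percentage within that range reflects the assumed curve, not the documents. This is an avoidable weakness that does not invalidate the study and is cheap to reduce.

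**What to change.** Leave the timing of CM as it is and change only the assessment schedule and its records:

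- Make the baseline call that is already planned before the first CM appointment after the consent visit, wherever feasible.
- Record three dates for each participant: consent, first CM contact after the consent visit, and baseline interview.
- Add one sensitivity analysis for the telephone outcomes, restricted to participants interviewed before any CM contact beyond the consent visit, or adjusted for the interval from CM start to interview.
- Name the timing of baseline in the Limitations section.
- As a precaution, state that the baseline ED-visit look-back windows end at the inclusion date.

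The cost is some earlier calls by the research team, a few date fields, one extra analysis and two sentences of text. One limit remains: the first evaluation in the ED will still precede the interview, so the change reduces the problem without removing it.
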